## Abstract

**Background:**

Lumbar microdiscectomy is the most commonly performed spinal surgery procedure, with over 300,000 cases performed annually in the United States alone. Traditionally, patients were advised to restrict post-operative activity as this was believed to reduce the risk of disc reherniation and progressive instability. However, this practice would often delay patients return to work. In contemporary practice many surgeons do not restrict patient post-operative activity due to the perception this practice is unnecessary. We describe a randomised controlled trial to assess the impact of activity restrictions on clinical outcome following lumbar discectomy.

**Methods/Design:**

The lumbar microdiscectomy and post-operative activity restriction trial is a multi-centre, randomised, controlled single blinded trial. Two hundred ten patients due to undergo single level lumbar microdiscectomy without a history of previous spine surgery, infection or fracture are randomised to be advised either restricted or unrestricted activity for a period of 30 days following lumbar microdiscectomy. Actual adherence with trial allocation will be monitored bioelectronically via a wearable device. Outcome assessment at follow up will occur at 1, 3, 6 and 12 months. The primary outcome will be a composite endpoint comprising changes in Visual Analogue Scale (Leg and Back), Oswestry Disability Index and the absence of intervertebral disc reherniation or secondary intervention.

**Discussion:**

This randomised controlled trial will directly compare post-operative protocols of activity restrictions and no restrictions following lumbar discectomy with adherence monitored bioelectronically.

**Trial Registration:**

Australian New Zealand Clinical Trials Registry: ACTRN12616001360404 (retrospectively registered 30/09/2016).

## Background

Lumbar microdiscectomy is the most commonly performed spinal surgical procedure [1]. Lumbar microdiscectomy is indicated for radicular pain unresponsive to conservative management (e.g. analgesia and physiotherapy), neurological deficit (e.g. weakness) or for cauda equina syndrome.

Lumbar microdiscectomy is minimally invasive, patients typically mobilize the same day and are discharged home the following day, making the operation suitable for day-procedure [2]. Traditionally following surgery, patients have been advised to restrict sitting, lifting or resuming other activities of everyday life, and are advised to either stand or lie for variable periods [3]. Sitting imposes greater intradiscal pressure than does standing [4] though evidence that increased pressure increases disc reherniation risk is lacking.

Such restrictions impact upon patients’ ability to return to work, travel or drive and basic comfort. It has been suggested that activity restrictions may also raise patient anxiety regarding reherniation risk. Moreover, neurosurgical practice regarding activity restriction varies, the dearth of evidence resulting in absence of clear clinical guidelines for surgeons, nurses, physiotherapists and occupational physicians. If no difference in outcomes are observed between groups in this randomised controlled trial future patients would be able to rapidly resume their normal activities, productivity, work and do so without fear or associated psychological morbidity. This would provide an evidence base to postoperative care and consensus amongst surgeons.

Two prospective studies published in the 1990s reported incidence of symptomatic recurrent disc protrusions and reoperation, and time to return to work in a cohort of patients whose movement was not restricted post lumbar microdiscectomy. Compared to rates in the literature among movement-restricted patients, adverse outcomes in this cohort were not considered higher [5, 6]. However, in the absence of a control group and randomisation, the evidence from such studies is relatively weak.

Bono et al. [7] recently published the first report of a randomised controlled trial investigating post-operative activity restrictions following lumbar discectomy. This trial compared post-operative protocols consisting of short (two weeks) and long (six weeks) periods of activity restriction following lumbar discectomy. The authors observed no significant difference in outcome as assessed by Visual Analog Scale (VAS) back or leg pain or Oswestry Disability Index (ODI). Disc reherniation rates differed between the groups observing short (11%) and long (7%) periods of activity restriction. This difference did not achieve statistical significance or translate into an appreciable difference in clinical outcome. However, the authors noted the study was underpowered to detect a significant difference in disc reherniation rate and calculated approximately 800 patients per arm would be required to achieve sufficient statistical power.

All previous studies on post-operative restrictions following lumbar discectomy have relied on self-reported adherence to mobility restrictions. Non-adherence is a well-recognized phenomena in spine surgery trials with non-adherence rates in SPORT approximately 40% at one year [8]. Such outcomes are likely to be biased. Contemporary wearable electronic devices that can accurately record the patient’s position (i.e. sitting/standing) enable empirical observation of patient adherence to a regimen of sitting restrictions with great reliability. This trial will be the first to track post-operative adherence to activity restrictions following lumbar discectomy and the impact of adherence on outcomes.

## Methods

### Question

Is the outcome of patients without restrictions inferior to those observing sitting and activity restrictions following lumbar discectomy?

#### Objectives

The study aims to determine whether the outcome of patients without imposed sitting and other behavioral restrictions post lumbar microdiscectomy are inferior to those of patients with imposed restrictions, in terms of disc reherniation, pain and disability outcome measures.

#### Design

The will be a randomised controlled surgeon and assessor-blinded trial. The trial design is illustrated in Fig. 1.

**Fig. 1 Fig1:**
[figure not shown]
Lumbar microdiscectomy and post-operative activity restrictions trial flow diagram

### Hypothesis to be tested

That movement restriction following first episode lumbar microdiscectomy in adults results in improved outcomes in disc reherniation rates, pain and disability outcome measures.

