#### Sample size

As detailed earlier one randomised controlled trial investigating the role of post-operative activity restrictions in outcome following microdiscectomy has recently been reported [7]. The authors recruited 108 patients and noted disc reherniation rates of 11% in the 2-week restriction group and 9% in the 6-week restriction group. Previous studies have indicated a reherniation rate ranging from 2 to 18% [16]. Annual reported reherniation rates have been closer to 4–5% in large series [8, 17, 18]. The authors of the randomised controlled trial calculated it would be necessary to have 800 patients in each arm in order to detect a statistically significant difference in disc reherniation rate and that this may not be feasible. We are in agreement with this assessment.

Reported rates of clinical success for lumbar discectomy vary widely dependent on the criteria. Using the criteria detailed in our composite primary outcome we would anticipate a clinical success rate within the broad range reported in the literature of approximately 70–90%.

In determining the power of this study, we assume that approximately 80% of patients will meet the definition of treatment success. The calculation of sample size can be based upon a threshold of a 20% difference in treatment success as clinically significant (i.e. 80% success vs. 64% success). In order to have 80% power to detect a 20% difference in the binomial outcome of treatment success defined at *p* = 0.05 the sample size calculated would be 78 patients per group. If we allow for an approximately 30% drop-out rate, this will bring the calculated sample size to 105 patients per group for a total of 210 patients in the trial.

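### Disc reherniation is posed as an outcome to be tested, and can be declared equivalent, in a trial whose own text accepts that it is far too small to settle it

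*Protocol article*

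**What the plan says.** The section on the hypothesis to be tested reads "That movement restriction following first episode lumbar microdiscectomy in adults results in improved outcomes in disc reherniation rates, pain and disability outcome measures". The Objectives section asks whether unrestricted patients fare worse "in terms of disc reherniation, pain and disability outcome measures".

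The Sample size section reports, from an earlier randomised trial, that "it would be necessary to have 800 patients in each arm in order to detect a statistically significant difference in disc reherniation rate". It passes on that trial's doubt whether so many could be recruited, and states its own position: "We are in agreement with this assessment". It then sizes the trial on composite treatment success (80% vs 64%), with 78 per group, raised to 105 for drop-out.

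Reherniation keeps three roles:
- one of five components of the composite (Primary endpoints);
- a secondary endpoint, as 12-month incidence of repeat surgery at the same level (Secondary endpoints);
- a hazard comparison between arms (Statistical analysis).

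The Statistical analysis section defines efficacy as 1 minus the hazard ratio. It deems arms equivalent when efficacy is below an absolute delta, for which it points to the sample size. The Background says that, if no difference in outcomes is seen, future patients could go back to normal activity quickly and without fear.

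**The concern.** The Objectives and hypothesis promise a test of reherniation rates. The Sample size section concedes that such a test is out of reach, and neither statement was adjusted to match. The only operative rule for reherniation then allows a verdict of equivalence, based on a delta that was set for a different endpoint.

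At stake is what a neutral result would be taken to mean. The Discussion gives reherniation, with instability, as the historical reason for restricting activity. A neutral composite, or a hazard ratio near 1, could be reported as showing that lifting restrictions leaves reherniation unchanged, when the data would be compatible with a doubling or tripling. This remains so even if the composite comparison is sound and correctly powered.

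**Working it through.** **Inputs from the protocol article.**
- 800 per arm for reherniation; 78 evaluable and 105 randomised per arm; 80% vs 64% composite success (Sample size).
- Rates in the earlier trial: "Disc reherniation rates differed between the groups observing short (11%) and long (7%) periods of activity restriction" (Background), but "disc reherniation rates of 11% in the 2-week restriction group and 9% in the 6-week restriction group" (Sample size).
- Base rate: "Annual reported reherniation rates have been closer to 4–5% in large series" (Sample size). The Primary endpoints section uses 5–10%.

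**Assumptions.** Two-sided 5% test (sidedness is not stated), normal approximation, 80% success in the comparison arm, other components unchanged.

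**1. The 800 per arm.** With m the mean of the two rates, n = [1.96·√(2m(1−m)) + 0.84·√(p₁(1−p₁) + p₂(1−p₂))]² / (p₁ − p₂)².
- 7% vs 11%: 803 per arm, so the figure reproduces.
- 9% vs 11%: 3,531 per arm. The pair of rates printed beside the 800 does not yield it; the Background pair does.

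**2. Power of the direct comparison, 7% vs 11%.** Power = Φ{[|p₁ − p₂|·√n − 1.96·√(2m(1−m))] / √(p₁(1−p₁) + p₂(1−p₂))}.

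| n per arm | Power |
|---|---|
| 78 | 14% |
| 105 | 17% |
| 800 | 80% |

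From a 5% base, 80% power needs a rise to about 17.1% at 105 per arm (3.4-fold) or 19.7% at 78 (3.9-fold).

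**3. Precision of the hazard ratio.** Expected events at 4–5%: 105 × 0.04 = 4.2 to 105 × 0.05 = 5.25 per arm, fewer after drop-out. With 5 vs 5 events, HR = 1 and the 95% interval is exp(±1.96·√(1/5 + 1/5)) = 0.29 to 3.45. With 4 vs 4 it is 0.25 to 4.0.

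**4. What the composite would show.** Take a doubling from 4.5% to 9%, modelled in two ways.
- (a) Every extra reherniation turns a success into a failure: 0.80 − 0.045 = 0.755. Power is 10% at 78 per arm and 12% at 105.
- (b) Success among patients without reherniation stays constant: 0.80/0.955 = 0.838, and 0.91 × 0.838 = 0.762. Power is 8% and 10%.

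**5. Rise needed to bring success down to 64% through reherniation alone.**

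| Base rate | (a) every excess counts | (b) constant success otherwise |
|---|---|---|
| 4.5% | 4.5 + 16 = 20.5% (about 4.6-fold) | 1 − 0.64/0.838 = 23.6% (5.2-fold) |
| 10% | 10 + 16 = 26% (2.6-fold) | 1 − 0.64/(0.80/0.90) = 28% (2.8-fold) |

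The 64% is the planning value, not a threshold below which every rise is missed. Under (a), with a 5% base, composite power at 78 / 105 per arm is 30% / 39% for a tripling and 56% / 69% for a fourfold rise.

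**6. The equivalence rule.** With 5 vs 5 events, efficacy is 1 − 1 = 0. That is below any positive delta, so the rule returns equivalence while the interval in step 3 reaches 3.45. The Sample size section expresses its difference as 20% relative, or 80 − 64 = 16 points absolute, in a success proportion. Neither is a margin for a reherniation hazard ratio, and no confidence limit enters the rule.

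**The case against.** The strongest defence is that the protocol is open about the limit. It says the earlier trial was underpowered for reherniation, accepts the 800, and explains that the composite was chosen because it needs smaller groups. The Objectives and hypothesis can be read as the composite put into words, since reherniation, pain and disability cover four of its five components. Reherniation is also kept and reported in its own right, and an interval around it is detail that an analysis plan not shown here may supply.

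Much of this stands, and it rules out several stronger readings.
- A reader might infer that reherniation is the leading question because it is listed first. List order is not rank, and no text calls it primary.
- A reader might infer that the composite replaces reherniation. That is true only of the endpoint used for sizing.
- A reader might infer concealment, or a claim that the composite stands in for reherniation. The text supports neither.
- A reader might take a four- to fivefold rise as the general figure. It belongs to a 4–5% base; at 10% it is about 2.6-fold. Recurrences treated by injection, or felt as pain, could also register under other components.

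What does not stand is the conclusion that the point is purely editorial. The hypothesis names reherniation rates and not the composite, and the equivalence rule is in the protocol's current text. An interval added in an analysis plan would not remove a rule that declares equivalence without one.

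**Conclusion.** The concern holds in this limited form. The Objectives and hypothesis include reherniation among the outcomes to be tested, the Sample size section accepts that this takes about 800 per arm, and the trial enrols 105. The composite, the secondary endpoint and the hazard comparison all leave the question open: about 14–17% power for 7% vs 11%, an interval reaching about 3.5 when five events occur in each arm, and about 8–12% composite power for a doubling from 4.5%. The equivalence rule could still turn such data into a finding of no difference.

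The sizes rest on the assumptions listed with the inputs and on the base rate. If lifting restrictions improved pain or disability, the composite could mask a larger rise than shown. The choice of a composite as the endpoint for sizing is not itself at fault. The fault is that the stated question and the equivalence rule go beyond what the trial can support.

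**What to change.** - Restate the Objectives and the hypothesis so that the confirmatory question is composite treatment success.
- Keep 12-month reherniation as an estimated safety outcome, reported beside the composite as a cumulative incidence difference (and hazard ratio) with its 95% confidence interval.
- Remove the equivalence verdict for reherniation from the Statistical analysis section.
- State in the analysis and conclusion text that neither a neutral composite nor a non-significant hazard comparison shows reherniation unchanged, and that the upper confidence limit is the largest excess the data do not exclude.
- Reconcile the 7% and 9% given for the longer-restriction group of the earlier trial, since only 7% vs 11% reproduces the 800.

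The cost is wording and one interval, with no more patients, visits or data. The downside is that the trial gives up a confirmatory claim on reherniation.

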#### Statistical analysis

Hazard of reherniation and of parenteral analgesia will be compared by treatment arms. Efficacy will be defined as 1 minus hazard ratio of active vs restricted arms. Efficacy less than absolute delta (see sample size) will be deemed equivalent. Change from baseline adjusted for baseline in functional scores will be compared across treatment arms. Magnitude difference will be compared using ranksum (Mann-Whitney-U) test.

Analysis will report both intention to treat and per protocol results. Per protocol adherence to treatment will compare time in movement by treatment arm using t-test allowing for differential variance**.** Time in movement should differ between arms. Two thresholds will be defined a priori – a sedentary level below which will be considered adherent to movement restriction, and an activity level above which non-restriction will be deemed to have occurred. These thresholds will be used to define adherence. In sensitivity analysis we will examine impact on trial outcomes of excluding those subjects allocated to restriction who moved above this threshold and those unrestricted who were sedentary. We will also conduct sensitivity analysis by cross allocating such subjects.

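### The protocol asks about inferiority, tests for a benefit of restriction and has no confidence-based rule on the primary endpoint, so a conclusion that no restriction is acceptable has no controlled error rate

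*Protocol article*

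**What the plan says.** Five places in the protocol article bear on what the trial is meant to show.

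- **Question:** "Is the outcome of patients without restrictions inferior to those observing sitting and activity restrictions following lumbar discectomy". The Objectives repeat this, asking whether outcomes without restrictions "are inferior to those of patients with imposed restrictions, in terms of disc reherniation, pain and disability outcome measures".
- **Hypothesis section:** the statement put to the test is "That movement restriction following first episode lumbar microdiscectomy in adults results in improved outcomes in disc reherniation rates, pain and disability outcome measures".
- **Sample size:** "In order to have 80% power to detect a 20% difference in the binomial outcome of treatment success", with 80% vs 64% as the example, "defined at *p* = 0.05 the sample size calculated would be 78 patients per group". The section does not state whether the test is one- or two-sided, or which arm has the 64%. After a dropout allowance of about 30%, it arrives at 105 per group.
- **Background:** "If no difference in outcomes are observed between groups in this randomised controlled trial future patients would be able to rapidly resume their normal activities".
- **Statistical analysis:** efficacy is 1 minus the hazard ratio (active vs restricted), set out with the comparison of reherniation and parenteral analgesia. Then: "Efficacy less than absolute delta (see sample size) will be deemed equivalent". The same section plans intention-to-treat and per-protocol results, adherence thresholds from the activity monitor, and sensitivity analyses that exclude or cross-allocate non-adherers.

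The Non-Adherence section says that explaining the clinical uncertainty at consent may lead to poor adherence in the restricted arm.

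**The concern.** The result most likely to change practice is that unrestricted patients do no worse. The hypothesis and sample-size wording aim at the opposite result, a detectable benefit of restriction. If that benefit is not detected, the protocol gives no valid route to the favourable conclusion. Non-significance is not evidence of similarity, and its frequency under a real deficit depends on power, not on a chosen alpha.

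The equivalence sentence does not fill the gap, for three reasons.

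- It concerns the hazards of reherniation and parenteral analgesia, not the composite.
- It uses a point estimate with no confidence bound.
- It takes its delta from a difference in success proportions and applies it to 1 minus a hazard ratio, which is another scale.

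Intention-to-treat dilution from non-adherence in the restricted arm would shrink a true benefit of restriction, and so favour the no-difference reading.

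**Working it through.** **Inputs.** From Sample size: 80% vs 64%, alpha 0.05, power 80%, 78 per group, about 30% dropout. From Treatment allocation: 1:1. From Background: about 40% non-adherence at one year in SPORT, used below only as an assumption.

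**1. The plan's own figure.** For a two-sided test, n = [1.96·√(2p̄(1−p̄)) + 0.842·√(p1(1−p1) + p2(1−p2))]² / (p1−p2)², with p̄ = 0.72. This gives 122.4, so 123 per group; one-sided, 97. Neither is 78. A non-inferiority calculation with 80% in both arms and a 16-point margin is n = (z_α + 0.842)² · 2(0.80)(0.20) / 0.16².

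- One-sided 5%: (1.645 + 0.842)² · 0.32 / 0.0256 = 77.3, so **78**.
- One-sided 2.5%: (1.960 + 0.842)² · 0.32 / 0.0256 = 98.1, so 99.

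The text describes one test and the number fits another.

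**2. Chance of a non-significant result when unrestricted care is truly worse.** Power = Φ[(d − 1.96·SE0)/SE1], where SE0 = √(2p̄(1−p̄)/n) and SE1 = √((p1(1−p1) + p2(1−p2))/n).

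| True rates | n per group | SE0 | SE1 | Power | Non-significant |
|---|---|---|---|---|---|
| 80% vs 64% | 78 | 0.0719 | 0.0707 | 0.606 | 39% |
| 80% vs 64% | 73 (105 × 0.7 = 73.5) | 0.0743 | 0.0731 | 0.578 | 42% |
| 80% vs 64% | 123 | 0.0573 | 0.0563 | 0.802 | 20% |
| 80% vs 70% | 78 | 0.0693 | 0.0689 | 0.301 | 70% |

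The step from 20% to 39% comes from the separate sample-size discrepancy, not from the framing.

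**3. What a non-significant result could still hide.** At 78 per group, 62 vs 52 successes (79.5% vs 66.7%) is a non-significant deficit of 12.8 points, with a 95% CI of about −1 to 27 points. That interval includes the protocol's own 16 points.

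**4. Effect of non-adherence (assumption: 40% of the restricted arm lose all benefit).** The restricted arm becomes 0.6 × 0.80 + 0.4 × 0.64 = 0.736, against 0.64.

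- Two-sided 5% test at 78 per group: SE0 = 0.0742, SE1 = 0.0738, power 0.252, so non-significant in about 75%.
- Intention-to-treat non-inferiority test with a 16-point margin at one-sided 2.5%: Φ[(0.16 − 0.096)/0.0738 − 1.96] = Φ(−1.09), about 14% false success. Without dilution this is 2.5% by construction.

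**5. The equivalence rule.** Read as signed, a hazard ratio of 2 gives efficacy 1 − 2 = −1, which lies below any positive delta and would be deemed equivalent. Read as |1 − HR|, it is still a point-estimate rule. At a 5% reherniation rate, 156 evaluable patients yield 7.8 events. The standard error of the log hazard ratio is about 2/√7.8 = 0.716, and exp(1.96 × 0.716) ≈ 4. The 95% interval therefore spans a factor of about four either way.

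**6. Non-inferiority power at 78 per group, 80% in both arms.** SE = √(0.32/78) = 0.0641.

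- 16 points: Φ(2.498 − 1.960) = 70% at one-sided 2.5%; Φ(2.498 − 1.645) = 80% at 5%.
- 10 points: Φ(1.561 − 1.960) = 35% at one-sided 2.5%.

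**The case against.** Much can be said for the protocol. The term non-inferiority is never used. Asking whether no restriction is inferior and hypothesising that restriction improves outcomes can be two sides of one directional claim, and sizing to detect a difference fits both. This stands: the Question and the Hypothesis alone could be reconciled. The clash comes when they are set beside the Background remark and the equivalence sentence, which claim something a difference test cannot give.

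A reader might infer that the protocol plans to treat a failed superiority test as proof of safety. It does not say so. The Background sentence is motivation, not a decision rule, and the article itself reports that the earlier randomised trial was underpowered for reherniation.

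A reader might also infer that the sample size is firmly a superiority calculation. The wording is, but 78 matches a 16-point non-inferiority design at one-sided 5%, so the intent is unclear.

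Setting 75% against 2.5% as the gain from a non-inferiority test would be unfair, because only the first figure includes non-adherence. Under the same dilution the intention-to-treat non-inferiority test errs about 14% of the time. The protocol says that poor adherence may occur, not that it is expected, and it already plans per-protocol and sensitivity analyses. Those analyses help, but no decision rule on the composite is attached to them.

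Finally, a margin might sit in an analysis plan that is not shown. That would not remove the conflict between statements in this article, nor repair the equivalence rule it prints.

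**Conclusion.** The point holds as a conflict of framing with a consequence for error control. As written, a conclusion that unrestricted care is acceptable would rest either on non-significance or on a point-estimate rule that does not cover the primary endpoint. Neither limits the chance of a false conclusion.

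Under a true 16-point deficit, a non-significant result occurs in about 39% of trials at 78 per group, or 20% if the trial had the size its stated inputs require. Under a 10-point deficit it occurs in about 70% at 78. These figures assume a two-sided 5% test and 80% success with restriction. The 75% figure further assumes 40% non-adherence with full loss of benefit. It shows the direction of the effect and is not a forecast. The documents do not support the stronger claim that the protocol has committed itself to reading non-significance as safety.

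**What to change.** State one framing and carry it through Background, Question, Objectives, Hypothesis, Sample size and Statistical analysis. If the aim is to support no restriction:

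- State a non-inferiority hypothesis on the difference in composite success. Justify the margin, and set it no larger than the 16 points that the Sample size section treats as clinically significant. Sixteen is an upper bound, not a recommended value.
- Conclude non-inferiority only if the confidence limit lies within the margin in both the intention-to-treat and the already planned per-protocol analyses. The second is needed because dilution weakens the first.
- Replace the point-estimate equivalence rule.
- State that a non-significant difference alone will not be read as no difference.
- Say which test the 78 per group serves, and restate power at the current size. For 16 points at 78 per group this is about 70% at one-sided 2.5% or 80% at 5%; for 10 points, about 35% at 2.5%. It is lower if both analyses must succeed.

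**Cost.** The changes are to wording and need no added patients, but the stated power becomes less favourable. Keeping 80% power for 16 points at one-sided 2.5% would instead need 99 evaluable per group, or 99/0.7 = 142 per group with 30% dropout.
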